# **Sample Size**

We plan to enrol 303 participants into the trial. As a key focus of this study is to investigate psychological and social mechanisms underlying the impact of DWM on mental health outcomes, we will implement a 2:1 allocation ratio (DWM to WLC) to ensure analyses are adequately powered. Based on previous research, we aim to detect a medium between-groups effect size (0.40) (Tol et al., 2020; Acarturk et al., 2020) on our main outcome measure (Kessler-10). With alpha of 0.05 and power of 80%, we will need to include a minimum of 224 participants across both arms (150 in the DWM arm and 73 in the WLC). We estimate 35% attrition given the mobile nature of the refugee population in Indonesia, and thus we will need to recruit 303 participants into the trial.

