**Trial Personnel:**

Facilitators will be responsible for conducting weekly DWM sessions with participants, via Zoom or phone calls. Facilitators are bilingual (English/Farsi) speakers with prior experience working with people from refugee backgrounds in Indonesia (e.g., previously working as teachers at refugee learning centers, staff in refugee-led originisations and/or interpreters for refugee-focused NGOs in Indonesia). Facilitators will receive 28 hours of in-person training by the research team. The in-person training covers: the DWM manual and techniques, general counselling/facilitation techniques, and responding to participant distress. Ongoing monitoring of facilitators’ capacity to practice will be conducted through regular supervision by a member of the research team who is a Clinical Psychologist. This oversight will help to ensure that any potential concerns about the capacity of the facilitators to carry out their roles is identified and addressed. Protocol adherence will be ensured by regular supervision of the facilitators and treatment fidelity checks using a checklist.

Assessors will be responsible for conducting the Structured Assessments with participants, via Zoom or phone calls. Assessors are bilingual (English/Farsi) speakers with prior experience working with people from refugee backgrounds in Indonesian (e.g., previously working as teachers at refugee learning centers, staff in refugee-led organisations and/or interpreters for refugee-focused NGOs in Indonesia). Assessors will receive 28 hours of in-person training by the research team. The in-person training covers: administering the instruments, general interview techniques, and responding to participant distress. Ongoing monitoring of assessors’ capacity to practice will be conducted through regular supervision by a member of the research team who is a Clinical Psychologist. This oversight will help to ensure that any potential concerns about the capacity of the assessors to carry out their roles is identified and addressed. Protocol adherence will be ensured by regular assessment fidelity checks using a checklist.

Supervisors are responsible for supervising the facilitators and assessors in the day-to-day running of the trial. Supervisors will hold at least Masters-level qualifications in Clinical Psychology.

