# **Statistics**

Data collected throughout the study will be analysed using hierarchical linear modelling or linear mixed models. Both intention-to-treat analysis (ITT; using all randomised participants) and completers’ (PP) analysis will be used.

Primary study parameters:

The main conclusion for study aim 1 (testing the efficacy of the DWM intervention, according to K10 scores) will be based on the ITT analysis of the primary outcome. A secondary analysis of the primary outcome will also be presented using the PP population. To estimate the treatment effect, data from Structured Assessments 1-4 will be used. A linear mixed model will be employed for the primary endpoint analysis, which will have treatment as fixed effects, baseline measurement of primary endpoint as covariate, and subject as random effects. The mean difference between two treatment arms at each visit/time together with its 95% confidence interval will be derived from the mixed model. Covariate-adjusted mixed model of primary endpoint will also be performed by adding pre-specified covariates at baseline (gender, age, education, traumatic experiences, and severity of symptoms) into the above model.

- Secondary study parameters: A linear mixed model as mentioned for the primary outcome analysis will be carried out for analysing the secondary outcomes (e.g., PTSD, Suicidal Ideation, Self-Identified Problems, Wellbeing, Functional Impairment, Digital Markers).

The main conclusion for study aim 2 (testing the mechanisms of change within the DWM intervention) will be based on the PP analysis, to ensure that only data from participants who received a sufficient ‘dose’ of the intervention are analysed. Cross-lagged panel analysis will be used to determine the temporal sequencing of psychological factors over the course of the intervention period, to test whether the hypothesised processes were mechanisms of change driving the intervention effects [hypothesis 2].

- The hypothesised mechanisms are: psychological flexibility (primary), emotion regulation, social satisfaction and functioning, and intolerance of uncertainty.

Missing data: Missing data will be treated as missing at random (MAR). No imputations of missing values will be made, as multilevel models can deal with missing data (Singer & Willett, 2003).

Other study parameters:

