- Treatment fidelity: In order to determine whether the intervention-as-implemented does not differ from the intervention-as-designed, fidelity checklists filled out by research assistants independent to the treatment facilitation team will be completed for a random sample, stratified on facilitator, of sessions/participants. Treatment fidelity will be analysed as a manipulation check.

Interim analysis (if applicable): Interim analyses will be considered in case safety issues are (suspected to be) violated.

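### DWM is delivered by several facilitators in one arm only, but the outcome model and sample size ignore facilitator; if outcomes cluster by facilitator, the confidence interval is too narrow

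*Protocol*

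**What the plan says.** The Statistics section specifies the primary analysis: a linear mixed model with treatment fixed, "baseline measurement of primary endpoint as covariate, and subject as random effects". The difference between arms at each visit and its 95% confidence interval come from this model. The covariate-adjusted version adds five baseline characteristics, none of them the facilitator. The secondary outcomes use the same model.

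On delivery, the Trial Personnel section states: "Facilitators will be responsible for conducting weekly DWM sessions with participants, via Zoom or phone calls". Each DWM participant receives five weekly calls (Trial Design; Trial Treatment). Waitlist participants have no facilitator; they receive only the workbook and audio files, after their last assessment.

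Facilitator enters the Statistics section once, under treatment fidelity, where checklists "will be completed for a random sample, stratified on facilitator, of sessions/participants".

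The Sample Size section targets a standardised effect of 0.40 with 2:1 allocation and states: "With alpha of 0.05 and power of 80%, we will need to include a minimum of 224 participants across both arms", split as "150 in the DWM arm and 73 in the WLC". It mentions no ICC or design effect.

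**The concern.** A subject random effect accounts for repeated K10 scores from the same person. It does not account for similarity between different people helped by the same facilitator. If some facilitators achieve more than others, DWM participants are not independent of one another, while waitlist participants are. A model without that level counts the DWM arm as carrying more information than it has.

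At stake is the main efficacy conclusion: an interval that is too narrow, a test that rejects too often, and power below the planned 80%. This is not a matter of detail left for a later document, because the protocol itself states the random-effects structure and that structure omits a level which the design creates.

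**Working it through.** **1. Reproduce the planned size.** Inputs from Sample Size: effect 0.40 SD, alpha 0.05 (two-sided reproduces the figure; one-sided would give 174), power 80%, ratio 2:1. With independent participants the normal formula gives 74 + 148 = 222, and the t-based version 75 + 150 = 225. The stated 224 is matched closely, so it assumes independence. Power at 150 versus 73 is 80.0% (normal) or 79.7% (t).

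**2. Variance with facilitators in one arm.** Let K be the number of facilitators and m = 150/K the DWM participants per facilitator. In SD units:

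- model as planned: V0 = 1/150 + 1/73 = 0.02037
- partially nested: V1 = [1 + (m − 1) × ICC]/150 + 1/73
- standard error ratio R = √(V1/V0)
- type I error of the planned test = 2 × [1 − Φ(1.96/R)]
- power with the correct error = Φ(0.40/√V1 − 1.96)

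K and the ICC are assumptions, because the protocol states neither. The ranges used are K from 4 to 20 and ICC from 0 to 0.10.

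**3. Worked case, K = 10, ICC 0.05.** m = 15 and the design effect is 1 + 14 × 0.05 = 1.70. V1 = 1.70/150 + 1/73 = 0.02503. R = √(0.02503/0.02037) = 1.109. Type I error is 7.7% and power 71.5%.

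**4. Range.**

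| K | ICC | Design effect (DWM arm) | R | Coverage of nominal 95% CI | Type I error | Power |
|---|---|---|---|---|---|---|
| any | 0 | 1.00 | 1.000 | 95.0% | 5.0% | 80.0% |
| 20 | 0.01 | 1.06 | 1.011 | 94.8% | 5.2% | 79.2% |
| 10 | 0.02 | 1.28 | 1.045 | 93.9% | 6.1% | 76.5% |
| 10 | 0.05 | 1.70 | 1.109 | 92.3% | 7.7% | 71.5% |
| 6 | 0.05 | 2.20 | 1.180 | 90.3% | 9.7% | 66.1% |
| 10 | 0.10 | 2.40 | 1.208 | 89.5% | 10.5% | 64.1% |
| 4 | 0.10 | 4.65 | 1.482 | 81.4% | 18.6% | 47.3% |

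R is how much larger the correct standard error is. R = 1.109 means that the model's value is 1 − 1/1.109 = 10% too small; R = 1.180 means 15% too small.

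**5. Check by simulation.** A two-sample comparison that ignores facilitator (150 versus 73, 10,000 runs per setting) rejected a zero average effect in 4.7%, 6.1%, 7.6% and 10.5% of runs for K = 10 and ICC 0, 0.02, 0.05 and 0.10. For K = 6 and ICC 0.05 it rejected in 9.8%. These agree with the formula.

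**6. Size needed.** At ICC 0.05 with K held fixed, 80% power needs 288 analysed participants for K = 10 and 369 for K = 6, against 222 without clustering.

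**The case against.** The strongest reply is that the harm is conditional. At ICC 0 the planned model is right, and several features may keep facilitator differences small: a self-help workbook with audio, 28 hours of common training, regular supervision and fidelity checks. With many facilitators and a low ICC the effect is about 1% of the standard error. This stands, and it limits the size that can be claimed.

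The type I error figures also need a particular null. Participants are individually randomised, so if DWM changed nobody's outcome, being assigned a facilitator would create no clustering. The inflated rates apply when facilitators differ but average to zero, and when the conclusion is meant for facilitators beyond those in the trial. If only these facilitators matter, the extra variance does not apply. This stands as a condition. A trial of a scalable programme would normally want the wider inference, but the protocol does not say which it intends.

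The calculation is a two-sample comparison, whereas the planned analysis adjusts for baseline and uses repeated measures. The ratio R does not depend on the SD, but the relevant ICC is that of the adjusted outcome, and the power figures are comparable only with the protocol's own 80%.

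The Statistics section opens by mentioning hierarchical models, and a separate analysis plan, which was not available, could add a level. But the section then spells out the model with subject only.

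Three stronger readings are not supported:

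- A reader might infer that 2:1 allocation makes the clustering worse. With the same 223 split 1:1 and ICC 0.05, K = 6 gives m = 18.58, design effect 1.879 and R = √[(1.879 + 1)/2] = 1.200, against 1.180 under 2:1. K = 10 gives 1.120 against 1.109. The planned allocation is slightly less affected.
- A reader might infer that stratifying fidelity checks by facilitator concedes correlated outcomes. It shows only that each facilitator is to be sampled.
- A reader might blame facilitators for all of a power loss calculated at 303 × 0.65 = 197 analysed. That number alone takes power to about 75%, which is a separate matter of attrition.

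**Conclusion.** The point holds in conditional form. The protocol fixes a model and a sample size that treat DWM participants as independent although several facilitators deliver the intervention in that arm only. For any facilitator ICC above 0, with inference beyond these facilitators, the standard error is too small and the interval too narrow.

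The size cannot be found from the protocol. Over the assumed range the correct standard error is 1% to 48% larger, and 11% to 18% larger at ICC 0.05 with 10 to 6 facilitators. The calculation also assumes that each participant stays with one facilitator and that caseloads are equal; the protocol states neither. It would be wrong to say flatly that the type I error exceeds 5%. What can be said is that the plan has no protection if facilitators differ, and no means of showing that they do not.

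**What to change.** Record which facilitator each DWM participant had, including any change. Fit a partially nested mixed model for the primary and secondary outcomes: a facilitator random effect in the DWM arm only, each waitlist participant as their own cluster, and small-sample degrees of freedom. Make it the primary model, or at least a pre-specified sensitivity analysis, and settle this before outcomes are compared by arm. Report the number of facilitators and the estimated ICC, and state in Sample Size that the 80% power assumes no facilitator clustering.

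The cost is one model term and one variable. The fidelity sampling already requires sessions to be linked to facilitators, although the protocol does not say that this link reaches the analysis dataset. If the ICC is not near 0 the interval will be wider, by roughly the ratios above and somewhat more once small-sample degrees of freedom are used. With few facilitators the variance will be estimated imprecisely, so the ICC should be given with its uncertainty.

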# **Data Ownership**

All research data collected during this trial is governed and handled following the Research Data Governance and Materials Handling [policy](https://www.gs.unsw.edu.au/policy/documents/researchdatagovernancepolicy.pdf). UNSW, rather than any individual or Organisational Unit, is the Custodian of data and materials and any information derived from the data. Original research data and primary materials generated in the research conducted at the University will be owned and retained by the University subject to any contractual, statutory, ethical, or funding body requirements.

# **Handling and Reporting Data**

Principal Investigators are responsible for maintaining adequate and accurate source documents and trial records that include all pertinent observations on each site's trial subjects. Source data must be attributable, legible, contemporaneous, original, accurate, and complete.

Trial subjects will be assigned a participant ID, and data will be reported using the [case report form]. Data reported on the [case report form], derived from source documents, should be consistent with the source documents, or the discrepancies must be explained. Any change or correction to a [case report form] should be dated, initialled, and explained (if necessary) and should not obscure the original entry (i.e., an audit trail should be maintained); this applies to both written and electronic changes or corrections.

1. Direct Access to Source Data and Documents

Site principal investigator(s) and institution(s) will permit trial-related monitoring, audits, IRB/IEC review, and regulatory inspection(s), providing direct access to source data/documents.

# **Monitoring Quality Control and Quality Assurance**

The Coordinating Principal Investigator and Principal Investigator(s) 'responsibility are to monitor the clinical trial. The Coordinating Principal Investigator and Principal Investigator(s) are responsible for undertaking or participating in site initiation or protocol-specific training before recruitment and data collection commences. A monitoring report demonstrating regular compliance monitoring with the clinical trial protocol, procedures, and HREC approval is provided to the UNSW Sponsor's Delegate annually.

Root, cause, analysis reports are to be completed by the Coordinating Principal Investigator for reports of non-compliance and serious breaches. A corrective and preventative action plan must be developed and actioned for any reports of non-compliance and serious breaches.

# **Clinical Trial Research Agreement**

The Coordinating Principal investigators must ensure that agreements are executed at each of the following sites before site initiation, recruitment, and data collection commences.

# **Research Governance Site Authorisation**

Site authorisation is to be obtained, or if a research site is added, a site authorisation letter from the delegated authority of an institution responsible for any participating site is obtained. It is to be stored as a GCP essential document before participants are recruited at a participating site.

# **Good Clinical Practice Requirements**

It is recommended that the Coordinating and Principal Investigators' ensure that all investigators and trial-related staff have current Good Clinical Practice Training. Once completed, the evidence of training confirmation is to be stored as a GCP essential document.

It is the responsibility of the Coordinating and Principal Investigators to familiarise themselves with the requirements of the [Guideline for Good Clinical Practice (E6, R2)](https://database.ich.org/sites/default/files/E6_R2_Addendum.pdf)

# **Essential Documents for the Conduct of a Clinical Trial**

All essential documents referred to in section 8.2 of the [Guideline for Good Clinical Practice (E6, R2)](https://database.ich.org/sites/default/files/E6_R2_Addendum.pdf)   are to be retained by all trial investigators.

**Task Key:**

| 1. Obtain informed consent * | 12. Sample collection |
| --- | --- |
| 2. Subject selection/recruitment* | 13. Sample processing and/or shipment |
| 3. Confirm eligibility (review inclusion/exclusion criteria)* | 14. Evaluate study-related test results * |
| 4. Obtain medical history (source documents) | 15. Use IWRS/IVRS |
| 5. Perform physical exam* | 16. Make entries/corrections on (e)CRFs |
| 6. Conduct study visit procedure as outlined in the protocol* | 17. Sign- off (e)CRFs* |
| 7. Make study-related medical decisions* | 18. Maintain essential documents |
| 8. Assess AEs/SAEs* | 19. Perform study-related assessments as per protocol * |
| 9. Dispense study drug* | 20. Complete company- specific log ( if applicable) |
| 10. Perform drug accountability | 21. Other (specify)____________________________________________ |
| 11. Study drug storage and temperature monitoring | 22. Other (specify) ____________________________________________ |

*These tasks may only be performed by qualified individual as permitted by local law, medical or standard of care practices, or applicable required training as per job description or designation.

# **Safety Monitoring Register Template**

- [UNSW Safety Monitoring Register Template](https://research.unsw.edu.au/document/UNSW%20Safety%20Monitoring%20Register%20Template.xlsx)
- [UNSW Adverse Event or Incident Event Case Report Form](https://research.unsw.edu.au/document/Adverse%20Event%20Incident%20Report%20Form%20September%202019%20.docx) Example.

